## Abstract

**Background:**

Lactation has a negative effect on female sexual function. Hormonal changes during lactation cause changes which might lead to dyspareunia, lack of libido, and anorgasmia. There are various pharmacological and non-pharmacological approaches to treat sexual dysfunction. While pharmacological treatment has multiple unwanted side effects, non-pharmacological therapies such as complementary medicine are a potential safer alternative. The aim of this study is to evaluate the effect of ear acupressure on sexual function of lactating women.

**Methods/design:**

This is a randomized clinical trial with a parallel sham control group. In this study, 76 lactating women between 6 months and 1 year after childbirth were referred to health care centers in Qazvin City and would be invited to participate. Participants will be divided into intervention (*n* = 38) and control (*n* = 38) groups using simple block randomization. Both intervention and sham control groups will be visited over 10 sessions within a 4-day interval. At each visit, the adhesives containing *Vaccaria* seed will be adhered for the intervention group, while non-latex-based adhesives with no *Vaccaria* seeds will be placed on the same ear acupoints for the sham control group. Selected ear acupoints include genitalia (two ear points), pelvic point, master shoulder, and posterior pituitary gland. The women will be asked to hold the seeds on their ears for 3 days and press each ear point three times a day for 20 s. After 3 days, they will be asked to remove the seeds from their ears and rest for 1 day. Sexual function as primary outcome in both groups will be assessed using the Female Sexual Function Index before and immediately after 1 and 2 months after the intervention. Also, Sexual Quality of Life as secondary outcome will be assessed using Sexual Quality of Life-Female (SQOL-F) before and 2 months after intervention. Data will be analyzed using repeated measure ANOVA at the significant level of 0.05.

**Discussion:**

This study is expected to support the impact of ear channel ear acupressure on sexual function in lactating women.

**Trial registration:**

Iranian Clinical Trial Registration Center IRCT20190626044028N1. Registered on 16 August 2019

## Background

The post-childbearing period is a crucial stage in the woman’s life that involves physical, hormonal, mental, social, and cultural changes [1]. Fatigue, insomnia, some stressors such as child care, and changes in the body image along with hormonal changes can reduce interest in sexual life and decrease the number of sexual intercourses during this period [1]. Endocrine function of lactation has a negative effect on sexual function, because prolactin decreases sexual hormones such as androgen and estrogen. This mechanism reduces sexual function because of vaginal dryness, vaginal epithelium atrophy, and dyspareunia [2]. About two thirds of women during lactating period experience at least one sexual problem, such as decreased libido, lack of sexual pleasure, dyspareunia, and vaginal dryness, which usually are resolved within 1 year after childbirth [3, 4]. The prevalence of sexual dysfunction increases from 19 to 63% in the prepartum period [5] to 34 to 91% in the postpartum period [6]. The results of various Iranian studies confirmed the high prevalence (31.5 to 85.4%) of sexual dysfunction during lactation [7, 8]. Therefore, sexual dysfunction is a common problem during lactation that needs more attention from health care providers.

In the post-childbearing period, most women try to return to their sexual life within 8 to 12 weeks after childbirth. However, it may take up to 1 year to resume sexual relationships with the same quality of before pregnancy [9]. Psychotherapy and pharmacotherapy are two main methods for treating female sexual dysfunction (FSD) [10]. However, the US Food and Drug Administration (FDA) does not recommend any foods or medicines for the treatment of FSD [11]. Therefore, non-pharmacological therapies such as complementary medicine are a potentially safer alternative to pharmacological therapy. Acupressure is one of the non-invasive complementary methods of traditional Chinese medicine (TCM) based on the principles of acupuncture [12]. Acupuncture stimulates medical points and meridians that are distributed throughout the body to regulate physiologic reactions [13]. Acupressure, like acupuncture, modulates a person’s vital energy by stimulating acupoints and meridians that are distributed throughout the body [14].

The external ear is one of the several somatotopic microsystems that can be used in acupressure. Ear acupressure, also known as auriculotherapy or auricular acupressure [15, 16], was first presented in ancient Chinese medicine (300 to 500 years BC), but [name] was the first Western physician who put forward auriculotherapy in a scientific way [13, 17, 18]. According to this theory, each part of the body is associated with a specific part of the ear that reflects the physiological or pathological state of the body [13]. In this method, the outer surface of the ear (auricle) can be stimulated to reduce pathological conditions in other parts of the body [13]. Ear stimulation can be performed in various ways such as manual finger pressure, electrical stimulation, lasers, different types of needles, magnetic seeds, and seeds to strengthen neural connections [18]. The World Health Organization (WHO) has recognized ear acupuncture as a promising therapeutic approach, because of its efficacy in managing health disorders [15]. Ear acupuncture has been recognized as a form of acupuncture that can affect all body organs [19]. Ear acupressure is an easy, non-invasive, and safe therapy [20, 21]. It is easy to use for mothers who need to take care of their child in the post-childbearing period [13].

There are several studies supporting the effects of ear acupressure on insomnia [20, 22], menstrual cramps and dysmenorrhea [21, 23, 24], premenstrual pain [25], chemotherapy-induced nausea and vomiting [26], smoking cessation [27], obesity [18], and shortness of breath [28]. However, the effect of ear acupressure on sexual function has not been studied.

### Research aim

This study is designed to investigate the effect of ear acupressure on the sexual function of lactating women.

## Methods

### Design and setting

This is a randomized clinical trial with a parallel sham controlled group. The study is designed in accordance with the CONSORT standards. Lactating women referred to health care centers in Qazvin City, Iran, will be invited to participate. Figure 1 shows the CONSORT flow diagram. The current protocol is organized based on the SPIRIT-TCM extension [29].

**Fig. 1 Fig1:**
[figure not shown]
The CONSORT flow diagram

### Participants

In this study, breastfeeding women between 6 months and 1 year after childbirth will be referred to health care centers in Qazvin City, Iran, and they will be invited to participate in the study. Inclusion criteria will be willingness to participate in the study, being literate, being primiparous, breastfeeding, full-term singleton delivery, lesion-free auricle, no ulcer and pain in the ear, and ability to present for all intervention sessions. Exclusion criteria will be being away from their spouse for more than 1 month, having complications during pregnancy, or having postpartum depression in the post-childbearing period. These criteria were diagnosed using the Edinburgh Postpartum Depression Scale, substance abuse in the individual or the spouse, and history of illnesses affecting sexual function in a woman or her spouse (e.g., premature ejaculation, cardiovascular, mental health disorders, thyroid diseases, any form of cancer, or injuries of the genital area). The use of drugs affecting sexual function such as psychotropic, cardiovascular, neurological, and hormonal drugs will also be excluded. After the initial screening, the Demographic and Obstetric Questionnaire and Female Sexual Function Index (FSFI) will be completed by the participants before any intervention.

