### Intervention

#### Ear acupressure group

The researcher will clean the auricle using 75% alcohol and then place *Vaccaria* seeds using non-latex-based adhesives on ear acupoints for genitalia, pelvis, shoulder, and the posterior pituitary gland. Figure 2 illustrates the intended ear acupoints. Intervention is designed for 10 sessions within a 4-day interval. During these sessions, the seeds are placed on the designated ear acupressure points. The women will be instructed to keep the seeds on their ears for 3 days, during which each point should be compressed three times a day for 20 s. The compression should be performed with moderate stimulation through pressing steadily and slightly tighter until feeling a slight tingling and discomfort. After 3 days, they will be asked to remove the seeds from their ears and rest for a day [29]. The women will be reminded daily by sending the text and will be reminded by phone for the next interventional session. This procedure will be performed for ten sessions for each participant. It should be noted that if a participant has problems during the use of the method for any reason (displacement of seeds, discomfort, etc.), she can remove the previous seed and ask the researcher to re-attach new seeds.

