#### Demographic and Obstetric Questionnaire

The demographic section includes questions such as age, education level, occupation, place of residence, economic status, age at marriage, and length of marriage. The obstetric section includes questions regarding the number of pregnancies, type of contraceptive method, delivery date, type of delivery, perineal injury, instrumental delivery, history of painful intercourse in prenatal period, infant gender, birth weight, first lactation, number of intercourse per month before pregnancy, onset of first intercourse after delivery, and average number of intercourses per week during lactation. Validity of this questionnaire will be confirmed by some of the faculty members of the midwifery department of Qazvin University of Medical Sciences, Iran.

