### Study procedure

After obtaining the necessary permissions from the Ethics Committee of Qazvin University of Medical Sciences, registration at the Iranian Clinical Trial Registration Center (IRCT), and obtaining the permission from Qazvin Nursing and Midwifery School, the researcher will attend for recruitment in Qazvin Health Centers. The lactating women of each center will be invited for participation. The process and purpose of the research will be explained to those who meet the inclusion criteria. Also, they will be ensured that their information will be kept confidential and that the questionnaires will be anonymous and coded in accordance with the research ethics. They will enter into the study after signing the written consent form. The researcher will ensure that they can leave the study at any time. After enrolling eligible individuals, a simple block randomization will be used. Participants will be randomly assigned to the intervention and control groups.

The questionnaires will be filled out by the participants before the intervention. Then, the intervention (acupressure) will be performed as mentioned above. Evaluation of sexual function in both the intervention and control groups will be performed using the FSFI questionnaire immediately, 1 and 2 months after the intervention. Figure 3 provides the timeline of recruitment, allocation, and assessment.

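### Many women will have their last visit after the first postpartum year, by which the protocol says these problems usually resolve; months since delivery, already collected, should be a prespecified covariate

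*Protocol article*

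**What the plan says.** **Entry.** The Protocol article, Participants, admits "breastfeeding women between 6 months and 1 year after childbirth". Breastfeeding is one of the inclusion criteria.

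**Treatment.** Under Ear acupressure group: "Intervention is designed for 10 sessions within a 4-day interval". Each cycle is 3 days with seeds and 1 day without: "After 3 days, they will be asked to remove the seeds from their ears and rest for a day".

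**Outcome visits.** Under Study procedure, sexual function is assessed "using the FSFI questionnaire immediately, 1 and 2 months after the intervention". The abstract (Methods/design) gives the secondary outcome as "Sexual Quality of Life-Female (SQOL-F) before and 2 months after intervention", so SQOL-F has a single post-treatment measurement. The Primary outcome section names no primary time point.

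**Natural course.** The Background describes sexual problems during lactation as ones "which usually are resolved within 1 year after childbirth", and adds that "it may take up to 1 year to resume sexual relationships with the same quality of before pregnancy".

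**Use of time since delivery.** The Demographic and Obstetric Questionnaire records the delivery date. Randomization and allocation describes blocks of four with no stratification by time since delivery. Statistical analysis describes a repeated measures ANOVA and names no covariate.

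**The concern.** The entry window closes at the same 1-year mark by which the protocol expects recovery, and follow-up runs on for more than 3 months. A woman who enters late is therefore measured when, on the protocol's own account, her problem has usually gone. A woman who enters at 6 months is measured while recovery is still under way. Time since delivery is thus a prognostic variable by the protocol's own reasoning. It is fixed before randomisation and its source is already on the baseline form, yet the stated allocation and analysis leave it out.

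The stake is precision. Differing stages of recovery add variance to the scores, women who have already recovered may have little left to gain, and with 38 per arm the two groups can differ by chance in months since delivery.

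**Working it through.** The article states neither a total follow-up length nor a share of women assessed after month 12, so it has no figure of its own to reproduce on this point. The sample size does not enter the timing.

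**Inputs from the article**
- Entry: 6 to 12 months after childbirth (Participants).
- Treatment: 10 sessions in 4-day cycles (Ear acupressure group).
- FSFI: end of treatment, then 1 and 2 months later (Study procedure).
- 38 women per arm, 76 in total (Sample size calculation).

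**Assumptions**
- One month is 365.25/12 = 30.44 days.
- Treatment starts at entry.
- Entry is uniform over the window, varied below.

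**Step 1: treatment length.** From the first to the tenth session is 9 × 4 = 36 days. To the end of the tenth cycle is 10 × 4 = 40 days.

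**Step 2: time to the last visit.** Two months are 60.9 days.
- 36 + 60.9 = 96.9 days = 3.18 months
- 40 + 60.9 = 100.9 days = 3.31 months

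**Step 3: postpartum age at the last visit.** Earliest 6 + 3.18 = 9.2 months; latest 12 + 3.31 = 15.3 months. The last visit falls after month 12 for women who enter later than 12 − 3.31 = 8.7 months (or 12 − 3.18 = 8.8 months).

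**Step 4: share after month 12 with uniform entry.** Share = months from entry to visit ÷ 6.

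| FSFI visit | Months from entry | Share after month 12 | Of 76 |
|---|---|---|---|
| End of treatment | 1.18–1.31 | 20–22% | 15–17 |
| 1 month later | 2.18–2.31 | 36–39% | 28–29 |
| 2 months later | 3.18–3.31 | 53–55% | 40–42 |

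**Step 5: other entry patterns, last visit, 40-day treatment.** Let the density of entry change linearly, with the density at month 12 equal to r times that at month 6. With s = 3.31/6 = 0.552, the share is [s + (r − 1)(s − s²/2)] ÷ [(1 + r)/2].

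| r | Share after month 12 |
|---|---|
| 1 (uniform) | 55% |
| 0.75 | 52% |
| 0.5 | 47% |
| 0.25 | 40% |
| 0 | 31% |

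For example, r = 0.5 gives [0.552 − 0.5 × 0.400] ÷ 0.75 = 0.47. Entry weighted to later months raises the share (r = 1.5 gives 60%). If the 2 months were counted from the start of treatment, the uniform share would be 2/6 = 33%, but the visit immediately after the intervention points to counting from its end.

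**Step 6: chance imbalance.** With uniform entry the SD of months since delivery is 6/√12 = 1.73. The standard error of the difference between arms is 1.73 × √(2/38) = 0.397, so the 95% range is ±1.96 × 0.397 = ±0.78 months.

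**The case against.** **The analysis plan is not shown.** It may already contain the covariate, and a condensed article need not list covariates. This stands to the extent that the article cannot be faulted for an omission. The entry window, the visit schedule and the stated natural course are protocol matters, however, and the covariate improves the stated analysis at almost no cost.

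**Randomisation protects the comparison.** A reader might infer that spontaneous recovery biases the result. It does not do so systematically: the sham arm is concurrent and recovers over the same period. Chance imbalance is already allowed for in the error rate of the test, and ±0.78 months is modest. This objection stands in full and confines the point to precision and dilution.

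**More than half is not established.** It needs roughly even entry and concerns only the last of three FSFI visits, none of which is named as primary. This too stands, so the share should be given as a range.

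**The Background sentence is general.** It gives no FSFI trajectory between months 9 and 15, and the repeated measures analysis with a pre-treatment score already absorbs stable differences between women. How much variance months since delivery would still explain is therefore unknown.

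Three further inferences are tempting but unsupported:
- *That the late outcome no longer describes lactating women.* The article gives no weaning rate, and 12 months after delivery is not the end of lactation.
- *That adjustment is worth a definite number of participants.* The usual factor 1/(1 − R²) only restates whatever R² is assumed, and the documents supply none.
- *That power collapses.* If the 2.38-point planning difference existed only in the 45% seen before month 12, the mean effect would be 0.45 × 2.38 = 1.07, and power about 27% with 34 per arm or 30% with 38. Nothing in the documents says that the effect vanishes at month 12.

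**Conclusion.** The point holds as a low-cost improvement, not as an error that threatens the trial's validity. The last FSFI and the only post-treatment SQOL-F fall 97 to 101 days after treatment starts, at about 9 to 15 months after delivery. The share of women then past the 1-year mark is about 53–55% with uniform entry and about 31–47% with entry weighted to earlier months (r from 0 to 0.5). Both rest on an assumed entry pattern and on treatment starting at entry. The comparison between arms is not systematically biased. Variance, dilution and chance imbalance are the costs, and the documents do not allow the first two to be sized.

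**What to change.** 1. Prespecify months since delivery at randomisation, derived from the delivery date already on the questionnaire, as a covariate alongside baseline FSFI in the primary between-group model. This costs one model term and no new data.
2. Record breastfeeding status at each FSFI visit and report it descriptively by arm. This costs one question per visit.
3. Label any analysis limited to scores obtained while breastfeeding as exploratory. It conditions on a variable measured after randomisation, so it does not keep the randomised comparison.

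Narrowing the entry window is not proposed. Keeping every last visit within month 12 would cut the window from 6 months to about 8.7 − 6 = 2.7 months, a recruitment trade-off that the documents give no basis for judging.

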### Role and qualification of practitioners

The research team consists of one specialist in auriculotherapy (TO), two specialists in reproductive health (ZA and NB), and one midwifery postgraduate student. The protocol of intervention was designed based on the literature review and expert opinion of TO who is an expert in auriculotherapy and is a journal editor for several international journals. Other team members have been qualified in this technique before designing present research. Participant screening and care providing will be done by SB, and ZA and NB will monitor her during the first 10 sessions to ensure the fidelity of providing intervention.

### Sample size calculation

Sample size is estimated according to the study of Bokaie et al. with the mean and standard deviation of total sexual function score has been reported as 24.65 ± 3.47 and 22.27 ± 3.03 in the intervention (telephone counseling group) and control groups, respectively [30]. Therefore, considering the first type error (α) = 0.05 (95% confidence), the second type error (β) = 0.2 (80% power) and error *d* = 5, and the possibility of 10% loss to follow-up, 38 individuals for each group are required. So, the total sample size will be 76 people.

### Intervention

#### Ear acupressure group

The researcher will clean the auricle using 75% alcohol and then place *Vaccaria* seeds using non-latex-based adhesives on ear acupoints for genitalia, pelvis, shoulder, and the posterior pituitary gland. Figure 2 illustrates the intended ear acupoints. Intervention is designed for 10 sessions within a 4-day interval. During these sessions, the seeds are placed on the designated ear acupressure points. The women will be instructed to keep the seeds on their ears for 3 days, during which each point should be compressed three times a day for 20 s. The compression should be performed with moderate stimulation through pressing steadily and slightly tighter until feeling a slight tingling and discomfort. After 3 days, they will be asked to remove the seeds from their ears and rest for a day [29]. The women will be reminded daily by sending the text and will be reminded by phone for the next interventional session. This procedure will be performed for ten sessions for each participant. It should be noted that if a participant has problems during the use of the method for any reason (displacement of seeds, discomfort, etc.), she can remove the previous seed and ask the researcher to re-attach new seeds.

**Fig. 2 Fig2:**
[figure not shown]
The selected ear acupoints

#### Sham control group

The control group will have sessions that will be the same as the intervention group except that no *Vaccaria* seeds will be placed on the ear acupoints.

### Measures

In this study, four measures will be used for data collection.

#### Demographic and Obstetric Questionnaire

The demographic section includes questions such as age, education level, occupation, place of residence, economic status, age at marriage, and length of marriage. The obstetric section includes questions regarding the number of pregnancies, type of contraceptive method, delivery date, type of delivery, perineal injury, instrumental delivery, history of painful intercourse in prenatal period, infant gender, birth weight, first lactation, number of intercourse per month before pregnancy, onset of first intercourse after delivery, and average number of intercourses per week during lactation. Validity of this questionnaire will be confirmed by some of the faculty members of the midwifery department of Qazvin University of Medical Sciences, Iran.

#### Female Sexual Function Index (FSFI)

It has been designed by Rosen et al. to evaluate sexual function in women over the past 4 weeks [31]. It consists of 19 items subdivided into six subcategories of sex desire (2 items), arousal (4 items), lubrication (4 items), orgasm (3 items), satisfaction (3 items), and pain (3 items). These subcategories have response ranges from 0 or 1 to 5, with higher scores indicating better sexual performance [32]. The questionnaire has been used in many studies abroad and has shown to have a high degree of internal consistency, reliability, and validity [33]. The findings of Fakhri and Mohammadi’s study showed that the Farsi version of FSFI, FSFI-IV, is a reliable and valid instrument with appropriate psychometric properties to evaluate women’s sexual function [32, 34]. Reliability of the scale has been calculated through stability analysis or calculation of the internal consistency coefficient. The Cronbach’s alpha coefficient was 0.70 and was higher for all domains and for the whole scale [34]. In addition, reliability was confirmed by the test-retest method and the correlation coefficient was reported high indicating that FSFI-IV is reusable within a 4-week interval [31, 35–38]. The maximum score for each domain is 6 and for the whole scale is 36. Also, any score less than 28 will be used to indicate sexual dysfunction [34].

